**3.2.5 Criteria for Terminating the Study**

Study termination may occur under the following circumstances:

(1) The subject experiences intolerable toxicity, and the investigator determines they are unsuitable to continue receiving the experimental drug.

(2) Significant errors are identified in the study protocol.

(3)The administrative department cancels the study.

Comprehensive suspension or termination of the study can be temporary or permanent. Please keep all study records for future reference in case of study suspension or termination.

**4 Drugs**

**4.1 Investigational drugs**

ASC22 is a monoclonal antibody drug for subcutaneous injection. The minimum packaging unit is a single-use glass vial made of brown neutral borosilicate, and each vial comes in a box. The drug is dosed at 1ml: 200 mg (1 ml/ampoule). ASC22 is manufactured by Alphamab Oncology, Jiangsu, China. It has been donated by Ascletis Pharma Inc., China. Storage conditions: Store between 2-8℃.

Chidamide tablets (Trade Name: Aipusha) are an HDAC inhibitor for oral administration. The drug specifications are 5 mg per tablet; each box contains 24 tablets. These tablets are manufactured by Shenzhen Chipscreen Biosciences, China, and have been provided free of charge by Ascletis Pharma Inc., China. Storage conditions: Keep in a light-shielding and sealed container store below 25°C.

**4.2 Antiviral regimen drugs**

ART treatment

**5 Clinical trial content**

**5.1 Sample size**

This study estimates that 12 participants will complete the trial, and the dropout rate will be controlled within 15%, so 15 participants are planned to be enrolled.

**5.2 Test Process**

This project is a prospective, single-center, single-arm clinical trial study. The plan is to enroll 15 PLWH. Following informed consent, each subject will receive a single dose of 1 mg/kg intravenous ASC22 on the first day, followed by a subcutaneous injection of ASC22 (drawing an appropriate volume of ASC22 according to the participant's needs and then injecting subcutaneously, with the injection speed not exceeding 0.06 ml/s). Additionally, oral chidamide intervention will be administered twice a week simultaneously, with a dosage of 10 mg.

Throughout this period, the ART treatment will be continued. The treatment period will last 12 weeks, and follow-up will extend until 24 weeks. Peripheral blood samples will be collected before the ASC22 intervention(every four weeks). Approximately 20 ml of blood will be collected during each session, and subjects will undergo medical evaluation concurrently.

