**Program summary**

| Basic information | Protocol Number: V20220703  Version/Date: V1.3/20220703  Study drug: Recombinant humanized PD-L1 single domain antibody Fc fusion protein injection  Drug code: ASC22 (previously used code KN035, Envafolimab)  Drug specifications: 1 ml: 200 mg (1 ml/ampoule)  Drug production unit: Alphamab Oncology, jiangsu, China |
| --- | --- |
| Title | Anti-PD-L1 antibody ASC22 in combination with chidamide as a “shock and kill” strategy for HIV functional cure: a phase Ⅱ study |
| Study purposes | Assessing whether ASC22 in combination with chidamide can reduce HIV reservoirs in PLWH with virologically suppressed |
| Study design | Single center, prospective, single-arm, phase Ⅱ study |
| Population | PLWH |
| Sample size | This study estimates that 12 participants will complete the trial, and the dropout rate will be controlled within 15%, so 15 participants are planned to be enrolled. |
| Study treatment | Participants received a subcutaneous injection of ASC22 (1mg/kg) once every 4 weeks for a total of 3 times. Chidamide (10 mg) was administered orally twice weekly for 12 weeks, while continue ART |
| Inclusion criteria | (1) Individuals diagnosed with HIV infection;  (2) Age ≥ 18 years old;  (3) BMI ≥ 18.0 to < 35.0 kg/m2;  (4) Capable and willing to comply with the time requirements for study visits and assessments;  (5) Currently receiving ART for at least 24 months, with two consecutive plasma HIV-1 RNA levels <50 copies/ml, separated by an interval of at least 12 months;  (6) During the screening period, CD4+ T cell count is ≥ 250 cells/µl (including the boundary value), and CD4/CD8 ratio is < 0.9;  (7) Agree to use contraception during participation in the project and for up to 6 months after the end of the trial;  (8) Willing to provide informed consent. |

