| **T cell immunek** | **×** | |  | **×** |  | **×** |  | **×** |  |  |  |
| **HIV Gag-specific CD8+T** | **×** | |  | **×** |  | **×** |  | **×** |  |  |  |
| **HIV reservoir**  **(HIV-1 DNA)** | **×** | |  | **×** |  | **×** |  | **×** |  |  |  |
| **ASC22 administration** |  | **×** |  | **×** |  | **×** |  |  |  |  |  |
| **Chidamide dispensing drug** |  | **×** | **×** | **×** | **×** | **×** | **×** |  |  |  |  |
| **Distribute medication diary cards** |  | **×** | **×** | **×** | **×** | **×** | **×** |  |  |  |  |
| **Recycling medication diary cards** |  | **×** | **×** | **×** | **×** | **×** | **×** | **×** |  |  |  |
| **AES** | **×** | | | | | | | | **×** | **×** | **×** |
| **Combination therapy** | **×** | | | | | | | | **×** | **×** | **×** |
| **Summary and analysis of test completion status** |  |  |  |  |  |  |  |  | **×** | | |

a. When the screening test and the day of drug administration coincide, relevant laboratory tests can be shared. Typically, results of pertinent safety tests conducted within approximately one week from the date of signing the informed consent form to the day of drug administration are acceptable.

b. Height measurement is only conducted during the screening period. Vital signs include body temperature, heart rate, respiration rate, and blood pressure.

c. ECG should be performed before ASC22 administration (within ±30 minutes) on the day of drug administration.

d. Blood routine tests include total WBC, WBC differential count (neutrophil [N] absolute count, lymphocyte [L] count, monocyte [M] count, eosinophils [E] count, absolute basophil [B] count), total RBC, HB, PLT, and HCT.

e. Blood biochemistry tests include total protein, albumin, total cholesterol, LDL, HDL, triglycerides, urea nitrogen/urea, uric acid, creatinine, alkaline phosphatase, lactate dehydrogenase, total bilirubin, direct bilirubin, indirect bilirubin, AST, ALT, calcium, phosphorus, magnesium, potassium, sodium, chloride, and serum amylase. Cardiac enzyme spectrum examination includes troponin-I, CK, and CK-MB.

f. Urine routine includes specific gravity, pH, urine sugar, protein, casts, ketone bodies, blood cells, and RBC.

g. Coagulation function includes PT, APTT, INR, FIB, TT, and D-dimer.

h. Thyroid function includes TSH, FT3, FT4, T3, T4. No relevant drug interference exists, and the test results within two weeks of the screening or baseline period are acceptable.

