**1.3 Preclinical Studies**

**1.3.1 Pharmacokinetics**

After a single subcutaneous administration of ASC22 in cynomolgus monkeys at doses of 5, 15, and 50 mg/kg, both the peak concentration (Cmax) and plasma exposure [AUC(0-t)] increased proportionally with the dose escalation in a 1:3:10 ratio. The average Cmax ratios were 1:4.13:12.53, and the average AUC (0-t) ratios were 1:3.24:12.01. ASC22 exhibited linear kinetic characteristics during metabolism in cynomolgus monkeys, and there were no significant gender-related differences in the main pharmacokinetic parameters. The average absolute bioavailability of ASC22 after subcutaneous administration was 104.62%. However, the half-life of ASC22 after a single subcutaneous administration was significantly shorter in the low and middle dose groups (low dose group: t1/2=31.30±24.85 h; middle dose group: t1/2=26.48±13.59 h) compared to the high dose group (t1/2=155.81±29.33 h). This difference may be attributed to immunogenic-positive animals in the low and middle-dose groups. After a single subcutaneous administration of ASC22 at doses of 5, 15, and 50 mg/kg, the immunogenicity positivity rates (D37) were 5/6, 4/6, and 0/6, respectively. Additionally, after intravenous administration of ASC22 at 15 mg/kg, the original positivity rate was 6/6.

In a multiple-dosing study conducted in cynomolgus monkeys, the dosing regimen consisted of once-weekly administrations for five doses, followed by a 4-week recovery period. The doses administered were 0, 5, 30, and 150 mg/kg. Following the first and last administrations, the average Cmax and AUC (0-t) of ASC22 in each dose group increased in response to the escalating dose. Notably, no significant accumulation was observed between the first and last administrations in male and female animals across the low, middle, and high dose groups. Only animals in the low-dose group tested positive for anti-drug antibodies after the dosing period and at the end of the recovery period, with positivity rates of 4/10 and 3/4, respectively.

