**3.1.2 Effectiveness Research**

**3.1.2.1 Anti-HBV Efficacy**

The ASC22 phase IIa clinical trial that has been conducted is a single-dose escalation study using three subcutaneous doses (0.3, 1.0, and 2.5 mg/kg, each dose injected to three patients) with 12 weeks of follow-up to explore the safety and efficacy of ASC22 in patients with CHB (ClinicalTrials.gov number: NCT04465890). The primary efficacy endpoint of the trial is the reduction of HBsAg at the 12-week follow-up after a single dose. Nine patients enrolled in the study with CHB had a median baseline HBsAg level of 3.0 log10 IU/mL.

Data from this Phase IIa clinical trial demonstrated a dose-dependent decrease in HBsAg after a single dose of ASC22 (0.3, 1.0, and 2.5 mg/kg, respectively). Eight of nine ASC22-treated patients showed some reduction in HBsAg at the end of the 12-week follow-up. One of three patients receiving the 2.5 mg/kg dose had a maximum decrease in HBsAg of 1.2 log10 IU/mL at 12 weeks of follow-up.

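### Section 5.2 makes the first ASC22 dose intravenous, while the synopsis and Section 4.1 make ASC22 subcutaneous, and no intravenous procedure or rationale is given

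*Protocol*

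**What the plan says.** Four places in the protocol bear on how ASC22 is given.

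- **Section 5.2, Test Process:** "each subject will receive a single dose of 1 mg/kg intravenous ASC22 on the first day, followed by a subcutaneous injection of ASC22". The technique that follows in the same sentence is for the subcutaneous route only: "injecting subcutaneously, with the injection speed not exceeding 0.06 ml/s".
- **Program summary, Study treatment:** "Participants received a subcutaneous injection of ASC22 (1mg/kg) once every 4 weeks for a total of 3 times".
- **Section 4.1, Investigational drugs:** "ASC22 is a monoclonal antibody drug for subcutaneous injection". The strength is 200 mg in 1 ml.
- **Table 1, flow chart:** the row headed "ASC22 administration" is marked at Baseline (Day 0), Week 4 and Week 8. It gives no route.

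**The concern.** Route of administration is a basic instruction for an investigational product, and the protocol gives two different routes for the first dose. Section 5.2 describes how treatment is delivered, so site staff could reasonably act on it. Its wording, intravenous and then subcutaneous, is coherent enough to read as a deliberate two-route regimen.

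At stake is the safety of the first dose in virologically suppressed people on ART. An intravenous dose of a PD-L1 inhibitor reaches its peak at once, whereas a subcutaneous dose is absorbed over days. A participant dosed as 5.2 says would receive the drug by a route for which the protocol gives neither human experience nor instructions.

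**Working it through.** **1. The texts side by side**

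| Place | Route of first dose | Number and timing |
| --- | --- | --- |
| Program summary | subcutaneous | 3 doses, every 4 weeks |
| Section 4.1 | subcutaneous product | not stated |
| Section 5.2 | intravenous, then subcutaneous | not stated for the subcutaneous part |
| Table 1 | not stated | Day 0, Week 4, Week 8 |

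No reading of 5.2 agrees with the synopsis on the route of the first dose. Table 1 agrees with the synopsis on number and timing but cannot decide the route. The Section 5.3 flowchart is not shown in the available text. Whatever it contains, it cannot remove a conflict between 5.2 and the other two sections.

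**2. How much dosing is affected**

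Planned enrolment is 15 (Section 5.1). With three doses each, 15 × 3 = 45 administrations are planned, of which 15 are first doses.

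- If 5.2 is read with Table 1 (one intravenous dose, then two subcutaneous), the total stays at 3 × 1 = 3 mg/kg.
- If 5.2 is read literally as an intravenous dose added to three subcutaneous doses, the total is 4 mg/kg. Table 1's three administrations make this the less natural reading.

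**3. Is there an intravenous procedure?**

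The only rate in 5.2 is the subcutaneous limit of 0.06 ml/s. Volume = weight × 1 mg/kg ÷ 200 mg/ml. The body weights are assumed.

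| Weight | Volume | Shortest time at 0.06 ml/s |
| --- | --- | --- |
| 50 kg | 0.25 ml | 0.25 / 0.06 = 4.2 s |
| 70 kg | 0.35 ml | 0.35 / 0.06 = 5.8 s |
| 100 kg | 0.50 ml | 0.50 / 0.06 = 8.3 s |

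The limit suits a small subcutaneous injection. It is not an intravenous rate, and the visible text supplies no diluent, infusion time or post-dose observation in its place.

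**4. Is there support for the intravenous route?**

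- The dose rationale in Section 3.1 makes no intravenous argument.
- The only other mention of intravenous ASC22 is in monkeys (Section 1.3.1): "after intravenous administration of ASC22 at 15 mg/kg".
- The one human ASC22 study whose route is stated, phase IIa in chronic hepatitis B (Section 3.1.2.1), used subcutaneous doses in 3 × 3 = 9 patients, 3 of them at 1.0 mg/kg.

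**5. Size of the early peak (illustration only)**

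In Table 2, the weekly 1 mg/kg column reads 233 ng/ml at 2 h, 2,690 ng/ml at 72 h and 3,137 ng/ml on day 8. The phase I route is not stated, but the slow rise fits absorption from an injection site. Assume that an intravenous dose first distributes into a plasma volume of 40 to 60 ml/kg, a figure that is not in the protocol. The initial level is then 1 mg/kg ÷ 60 ml/kg = 17 µg/ml up to 1 mg/kg ÷ 40 ml/kg = 25 µg/ml. Against the highest value in that column, 17 / 3.137 = 5.4 and 25 / 3.137 = 8.0, so about 5 to 8 times as high.

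**The case against.** The strongest reply is that this is a wording slip that nobody would follow. The protocol shows loose translation elsewhere: Table 1, for example, heads the post-treatment visits as a screening period. The synopsis, the product description and the technique in the very sentence at issue all point to subcutaneous dosing, and nothing gives 5.2 precedence over them. That a slip is likely stands. It does not make the sentence safe, because the route should not have to be inferred.

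The harm can also be argued down. The illustrative peak of 17 to 25 µg/ml is close to the 23.8 µg/ml in Table 2 at 72 h in the weekly 5 mg/kg group. Section 3.1.3 reports no dose-limiting toxicity among those assessed at 0.01 to 10 mg/kg. Subcutaneous bioavailability in monkeys was 104.62%, so total exposure would barely change. This stands too, and it narrows the concern to the immediate peak, acute tolerability and the suitability of a subcutaneous product for intravenous use.

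Finally, most human studies in the protocol do not state a route. These include phase IIb with 74 participants at 1.0 mg/kg. The 103-patient tumour study reports injection-site reactions, which suggests injection. The absence of human intravenous data is therefore partly silence. But silence is not support, and an intravenous first dose would need support.

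**Conclusion.** The concern holds. Section 5.2 contradicts the Program summary and Section 4.1 on the route of the first dose, and Table 1 does not resolve it. Taken literally, it changes the first dose for all 15 planned participants, 15 of 45 administrations, with no intravenous instructions or rationale.

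The synopsis and Table 1 agree on dose count and interval, so those are not in dispute. The total of 3 mg/kg rests on reading 5.2 together with Table 1. The contradiction itself needs no assumption; the body weights and plasma volume are assumed and serve only to illustrate. It must be corrected because it is a wrong route in a dosing instruction.

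**What to change.** Replace the sentence in Section 5.2 with: *1 mg/kg ASC22 subcutaneously on Day 0, Week 4 and Week 8 (three doses in total)*. Keep the existing subcutaneous technique and speed limit. This settles route and count together. Add the word *subcutaneous* to the ASC22 row of Table 1.

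If an intravenous first dose is truly intended, justify it, specify preparation, infusion rate and post-dose observation, and state it consistently in the synopsis, Section 4.1 and Table 1.

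The cost is one corrected sentence and one added word, plus the ethics committee resubmission that Section 10.1 requires for any revision. No extra participants, visits or procedures are needed.

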**5.3 Flowchart Of The Study**

[figure not shown]

**Figure 2 ASC22 clinical trial flow chart**

**5.4 Test Result**

**5.4.1 Security Monitoring**

The related symptoms and laboratory tests need to be monitored. These symptoms may include vomiting, fatigue, rash, itching, diarrhea, constipation, borborygmi, fever/chills, headache, palpitations, heat sensation, changes in appetite, gastrointestinal pain, gastroesophageal reflux, touch sensitivity, taste and smell disturbances, dizziness, muscle or joint pain, blisters, oral lesions, conjunctivitis, facial edema, and more.

The severity of AEs will be graded according to the CTCAE version 6.0. AEs are defined as any adverse medical events occurring in patients or clinical research participants taking a drug product, regardless of causality with the treatment. The investigator will assess the relationship of each event to the study drug as either reasonably likely or not reasonably likely. AEs are divided into grades 1-5, with grade 3 being serious but not life-threatening and requiring hospitalization, grade 4 being life-threatening and requiring hospitalization, and grade 5 indicating an AE-related death requiring immediate intervention.

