| Primary outcomes | The primary outcomes were assessed by quantifying changes in cell-associated (CA) HIV RNA, total HIV DNA, integrated HIV DNA in PBMCs, and plasma HIV RNA, as well as by analyzing variations in the functionality of HIV Gag- and Pol- specific CD8+ T cells from baseline to post-treatments. In addition, changes in CD4+ T cell counts, CD8+ T cell counts, and CD4/CD8 ratios were monitored at baseline and at different time points during treatment. |
| Secondary endpoints | The related symptoms and laboratory tests need to be monitored. These symptoms may include vomiting, fatigue, rash, itching, diarrhea, constipation, borborygmi, fever/chills, headache, palpitations, heat sensation, changes in appetite, gastrointestinal pain, gastroesophageal reflux, touch sensitivity, taste and smell disturbances, dizziness, muscle or joint pain, blisters, oral lesions, conjunctivitis, facial edema, and more.  The laboratory tests include blood routine, liver and kidney function, urine routine, myocardial enzymes, blood sugar, blood coagulation, electrolytes, electrocardiogram, chest CT examination, cardiac ultrasound examination, and abdominal B-ultrasound for liver and kidney examination.  The severity of AEs will be graded according to the CTCAE version 6.0. AEs are defined as any adverse medical events occurring in patients or clinical research participants taking a drug product, regardless of causality with the treatment. The investigator will assess the relationship of each event to the study drug as either reasonably likely or not reasonably likely. AEs are divided into grades 1-5, with grade 3 being serious but not life-threatening and requiring hospitalization, grade 4 being life-threatening and requiring hospitalization, and grade 5 indicating an AE-related death requiring immediate intervention. |
| Statistical Analysis | Statistical analyses were carried out using GraphPad Prism 8.0 (San Diego, CA, USA) and SPSS 15.0 statistical software (Chicago, IL, USA). P-value (P) below 0.05 was considered statistically significant. |

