**3.1.3 Security**

Until May 2, 2018, participants who completed the DLT assessment in the 0.01-10 mg/kg dose groups of the Phase I anti-cancer studies conducted in the US and China had no experienced DLTs. Similarly, no DLTs occurred in any paticipants who completed the DLT assessment in the Japanese Phase I study's 1.0-5.0 mg/kg dose group. Drug-related AEs observed across these studies were primarily of grade 1-2. There was no positive correlation between the incidence of study drug-related adverse events and the administered drug dose. Notably, only one drug-related grade 3 or higher AEs occurred in the studies in China and the US. The study in China showed grade 3 autoimmune dermatitis in the 0.3 mg/kg dose group, which resolved after 33 days of drug intervention. The study in the US showed grade 3 lymphopenia in the 0.1 mg/kg dose group, which was decided after one week without drug intervention. In summary, ASC22 demonstrated a high level of safety and good tolerability among all enrolled subjects in the 0.01-10 mg/kg dose group.

ASC22 has conducted a Phase IIa/IIb clinical study in CHB. Phase IIa comprised a single-dose escalation involving three dose groups of 0.3 mg/kg, 1.0 mg/kg, and 2.5 mg/kg, each with three participants. On the other hand, Phase IIb is a multiple-dose study, with selected dose groups of 1.0 mg/kg and 2.5 mg/kg. Each group receives 12 administrations, administered once every two weeks. The Phase IIa clinical study was completed on June 7, 2021, with participants exhibiting good safety profiles, and all AEs were of grade 1. In the Phase IIb study, 74 participants were enrolled in the 1.0 mg/kg group, and 48 participants were enrolled in the 2.5 mg/kg group. It is currently ongoing for Phase IIb study.

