**6 Efficacy and safety outcomes**

The primary outcomes were assessed by quantifying changes in CA HIV RNA, total HIV DNA, integrated HIV DNA in PBMCs, and plasma HIV RNA, as well as by analyzing variations in the functionality of HIV Gag- and Pol- specific CD8+ T cells from baseline to post-treatments. In addition, changes in CD4+ T cell counts, CD8+ T cell counts, and CD4/CD8 ratios were monitored at baseline and at different time points during treatment.

Safety Outcomes: number of participants experienced with drug-related AEs of Grade 3 or Higher.

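### The protocol gives two rules for grade 3 and 4 adverse events, CTCAE and a scale requiring hospitalization, and does not say which one sets the grade 3 or higher safety count

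*Protocol*

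**What the plan says.** Section 5.4.1 names a standard: "The severity of AEs will be graded according to the CTCAE version 6.0". Later in the same paragraph it describes the five grades itself, "with grade 3 being serious but not life-threatening and requiring hospitalization, grade 4 being life-threatening and requiring hospitalization". Grade 5 is described as a death that calls for immediate intervention. The Program summary, under secondary endpoints, has the same text: "AEs are divided into grades 1-5, with grade 3 being serious but not life-threatening and requiring hospitalization". Neither place says whether the description restates CTCAE or replaces it.

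Section 6 applies the threshold: "Safety Outcomes: number of participants experienced with drug-related AEs of Grade 3 or Higher". The secondary endpoint in the Program summary contains no count or cut-off. It opens with "The related symptoms and laboratory tests need to be monitored" and goes on to list symptoms and tests.

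On relatedness, Section 5.4.1 has the investigator judge each event against the study drug, in the singular. The Program summary gives the PD-L1 fusion protein (ASC22) as the study drug. Section 4.1 lists both ASC22 and chidamide under investigational drugs.

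**The concern.** A severity grade says how bad an event is. Hospitalization says how it was handled and is normally part of the seriousness assessment. The protocol's description merges the two: grade 3 is called serious, and admission is joined to grades 3 and 4 by the word and, which makes it a condition of the grade.

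Table 1 schedules blood counts and biochemistry (including liver enzymes, amylase and creatine kinase) at every visit. A markedly abnormal value found this way need not lead to admission. Under the literal description it would then fail the grade 3 condition and fall out of the Section 6 count. Two investigators, or one investigator on two occasions, could grade the same event differently and both be following the protocol.

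With 15 participants, no control arm and one safety count, one or two reclassified participants change the safety message. The singular study drug adds a second ambiguity to the same count: an event attributed to chidamide alone could be read as outside it.

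**Working it through.** **1. The passages side by side**

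| Place | Rule for grade 3 | Hospitalization required? |
|---|---|---|
| 5.4.1 and Program summary, CTCAE sentence | the named external scale | not stated in the protocol |
| 5.4.1 and Program summary, description of grades | severe, not life-threatening, and hospitalized | yes, as written |
| 6, safety outcome | grade 3 or higher, drug-related | depends on which rule is used |

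The description stands in two places, so it is not an isolated slip. No sentence ranks the two rules.

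**2. Direction**

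Let A be the set of participants with a drug-related event severe enough for grade 3 or higher without regard to admission, and B the subset of A whose qualifying event also involved hospitalization. B lies within A, so the count under the added condition is at most the count without it. The direction follows from the wording alone.

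**3. The plan's own figure**

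The point disputes no figure. The enrolment used below reproduces: Section 5.1 gives 12 completers and dropout within 15%, and 12 / (1 − 0.15) = 14.12, rounded up to 15.

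**4. Illustration of size**

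Inputs:
- n = 15 (Section 5.1).
- p = 16/103 = 0.155, the grade 3 to 4 drug-related rate with ASC22 monotherapy in advanced solid tumours (Section 3.1.3, which reports no related grade 5 events). That it carries over to this trial is an assumption.
- h = share of affected participants whose qualifying event involved hospitalization. The protocol gives no value, so a range is shown.

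Formulas, with participants independent: expected count = n × p × h; P(none) = (1 − p × h)^n.

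| h | p × h | Expected of 15 | P(none) |
|---|---|---|---|
| 100%, or no hospitalization condition | 0.155 | 2.33 | 0.08 |
| 75% | 0.117 | 1.75 | 0.16 |
| 50% | 0.078 | 1.17 | 0.30 |
| 25% | 0.039 | 0.58 | 0.55 |
| 0% | 0 | 0 | 1.00 |

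**5. What one or two participants mean at this size**

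The exact 95% interval is 0 to 21.8% for 0/15 and 1.7% to 40.5% for 2/15. Moving two participants across the threshold nearly halves the upper limit.

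**The case against.** The best defence is that CTCAE is named first, as the operative rule. The later sentence can be read as a loose gloss: it does not describe grades 1 and 2 and does not tell anyone to downgrade an event. An investigator who follows the CTCAE sentence would still record a grade 3 event without admission. This stands against a stronger reading that a reader might infer, namely that such events will be dropped or recorded as grade 2. The documents show only that they can be.

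A reader might also infer a proven clash with CTCAE's laboratory thresholds. The CTCAE text is not in the documents, so that cannot be checked here, and the point does not need it.

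Nor is Section 3.1.3 proof. "The study in the US showed grade 3 lymphopenia in the 0.1 mg/kg dose group", and the event was over in a week without drug intervention, but the section does not say whether that patient was admitted or how that study graded events. It is suggestive only.

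The magnitude is borrowed. The same section reports that all adverse events were grade 1 in the phase IIa chronic hepatitis B study. With nine patients and single doses this is weak evidence, but it points to a lower rate than the oncology figure.

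The consequence is also bounded. No test, stopping boundary or dose rule uses the grade threshold, adverse events are defined regardless of causality and collected throughout, and laboratory results are reported in their own right. So the abnormality stays in the data even if the count misses it. What remains is the headline safety count, which has no settled definition.

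Finally, replacing drug-related events by all treatment-emergent events would be a preference and is not argued here. Saying which drugs the word drug-related covers is a matter of definition.

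**Conclusion.** The inconsistency is real and should be corrected. Section 5.4.1 and the Program summary each contain two grading rules, and the protocol does not say which defines "number of participants experienced with drug-related AEs of Grade 3 or Higher". If the written description is applied, the count can only fall or stay the same.

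How far it would fall cannot be derived from the protocol. Under the borrowed 15.5% rate and n = 15, the expected count lies anywhere between 2.33 and 0, depending on an unknown hospitalized share. These figures show that the wording could matter at this sample size. They do not estimate an undercount.

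The documents do not establish that events will be lost, or that the combination will necessarily look safer than it is. The scope of drug-related is also unsettled, because the Program summary names one study drug and Section 4.1 lists two investigational drugs.

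**What to change.** - In Section 5.4.1 and the Program summary, delete the hospitalization wording from the descriptions of grades 3 and 4, so that the named CTCAE scale alone defines grade 3 or higher in Section 6. Remove the word serious from the grade 3 description for the same reason.
- Record seriousness, including hospitalization, in a separate case report form field.
- In Section 6, state that drug-related means related to ASC22, to chidamide or to both, and align the singular study drug in Section 5.4.1 with Section 4.1.

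The cost is protocol and case report form wording, with no change to visits, sample size or assessments. The reported grade 3 or higher count may become slightly less favourable.
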